# HIV TESTING OF PARTICIPANTS WITH UNKNOWN HIV STATUS (SUB-STUDY 1)

In our VMMC program and in other Kenyan programs as well, between 10% and 30% of men decline HIV testing. Given that VMMC is offered principally as an HIV prevention strategy, it is important to determine the HIV status of those who decline testing, and if the prevalence is significantly higher than those who accept testing, there will be need to design approaches to improve uptake of testing. This is particularly important following results from a recently concluded study that indicated that 44% of HIV-infected men resumed sex before the recommended 6 weeks of sexual abstinence^[[27]](#endnote-26)^.We will identify this group from the MOH VMMC Client Form, Version 2, May 2011 (Appendix 23: MoH VMMC Client Form). According to the MOH guidelines, anyone who is not tested on site and does not report being HIV+ is assumed to have unknown HIV status. This will be our population of interest, and will be identified if under Section B of the client form, item B1, question 2 (HIV status by self report) “Unknown” or “HIV” box is checked. While the section of the form is filled by the Counselor performing the test, the document moves with the client through subsequent stages and will be reviewed by the clinical staff performing physical exam (who will administer the written consent, Appendix 24 Written ICF for Unlinked HIV Testing on Blood Sample collected from Bleeding Vessels of Participants with Unknown HIV Status) as well as those performing the surgery (who will collect the blood and therefore need to identify eligible participants).

Sample size for HIV prevalence among uncircumcised men whose HIV status is unknown (*Sub-study 2*)

Currently in Kenya, there are no anonymous and/or unlinked HIV prevalence studies that evaluate the rates of HIV among uncircumcised men whose HIV status is unknown which can inform sample size estimation. We are also unaware of similar studies in other parts of Africa. However, studies from developed countries suggest that those whose HIV status is unknown may be at greater risk for HIV infection than those who accept testing.^[[28]](#endnote-27),^^[[29]](#endnote-28)^ Recently, researchers in Washington D.C, USA, tested de-identified blood samples from decliners of HIV testing. They found that the rate of HIV infection was nearly three-times higher in those who declined routine ED HIV testing compared with those who accept such testing.^38^ A similar finding had earlier been found in Atlanta-USA where patients who declined testing were three times more likely to be HIV infected than those patients who were tested.^39^ In Luxemburg-Netherlands, heterosexuals with a history of STI, current STI-related complaints, and those who had been warned that their partners were diagnosed with STI were more than two times as likely to refuse HIV testing.^[[30]](#endnote-29)^

Data from our VMMC programs that target older men in most (12/14) of the districts of Nyanza province inhabited by non-circumcising Luo community suggest that the prevalence of HIV among men taking up VMMC and who accept testing is 10.8%. These data also suggest that 23.6% of the men in the target age-group who accept VMMC decline HIV-testing. To be conservative, we assumed that the prevalence of HIV in this group of men is around two times that of similar men who accept such testing, translating into 21.6% HIV prevalence among uncircumcised men whose HIV status is unknown. If our assumption of twice the prevalence is wrong, we believe we shall have erred on the side of safety - we shall have erred on the side of over-estimating rather than underestimating the required sample size thus ending up with a bigger sample size than would have needed. However, we will benefit immensely in terms of precision of the study estimates. Using a design effect of 2.5 due to clustering, in the sample size for estimating prevalence^41^, we estimated that we will need to test randomly selected unlinked blood samples from 163 men per arm whose HIV status is unknown in order to estimate a HIV prevalence that falls within 10% points of the true population prevalence with 95% confidence. Our study staff will collect samples from all of men who refuse testing but consent to Unlinked HIV testing. Binkin et al. (1992)^41^ found that for a relatively common disease (as is HIV in the study area), if the desired level of precision is around ±10% points or less and the design effect is around 2, then collecting data from more than 30 clusters provides good estimates of the true (unknown) population parameters with the desired level of precision. Our study will be conducted in 45 clusters.

With a refusal rate of 23.6% voluntary HIV testing, and a consenting rate of 60%, then the rate of getting a man who refuses testing but consents to the testing of unlinked blood sample from his bleeding vessels is 14.2%.   In other words, of the 4932 participants in the main study we expect 1164 (4932*0.236) to refuse HIV testing. With assumed unlinked HIV testing acceptance rate of 60%, we can obtain 700 such men from our sample size of 4932 in the main study. For a design effect of 2.5, using a sample size of 700 for the sub-study will enable us to estimate the HIV prevalence of 21.6% with a precision of  4.8%=sqrt[(2.5*1.96^2*.216*.784)/700].

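### The HIV sub-study presents a two-fold prevalence ratio as safe for sample size, but the three-fold ratio it cites needs 211 men per arm, not 163

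*Protocol*

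**What the plan says.** The passage is the sample-size text for the HIV-prevalence sub-study, in the Protocol section on HIV testing of participants with unknown status (labelled Sub-study 1 in the section heading and Sub-study 2 in the sample-size sub-heading).

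- **Base rate.** Program data suggest that "the prevalence of HIV among men taking up VMMC and who accept testing is 10.8" per cent.
- **Assumed ratio.** The authors choose a factor of two: "To be conservative, we assumed that the prevalence of HIV in this group of men is around two times that of similar men who accept" (HIV testing is meant). Twice 10.8% gives the planning value of 21.6%.
- **Cited evidence.** The preceding paragraph reports a Washington, D.C. study: "They found that the rate of HIV infection was nearly three-times higher in those who declined routine ED HIV testing". It also reports an Atlanta study in which decliners were three times as likely to be infected.
- **Direction of error.** If the two-fold assumption is wrong, the authors believe that "we shall have erred on the side of over-estimating rather than underestimating the required sample size".
- **Result.** With a design effect of 2.5, the calculation calls for "randomly selected unlinked blood samples from 163 men per arm whose HIV status is unknown". The target it serves is a margin of ±10 percentage points at the 95% level.
- **Expected yield.** About 700 men, with a stated precision of 4.8 points at 21.6%.

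**The concern.** The sample size is set by a fixed absolute margin. Under that criterion the required number follows the binomial variance p(1−p), which grows as prevalence rises towards 50%. All the prevalences in play lie below 50%, so a lower assumed ratio gives a smaller sample.

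The protocol cites ratios of about three, adopts two, calls the choice conservative, and says an error would leave the sub-study too large. For an error in the direction of its own evidence, the opposite is true. A reader judging whether the sub-study is large enough would rely on a protection that does not exist. At stake is whether the stated precision, above all the per-arm ±10 points, would be reached if decliners carry the excess HIV prevalence that the cited studies describe.

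**Working it through.** **Inputs**, all from the sub-study's sample-size text: prevalence in acceptors 10.8%; assumed ratio 2; cited ratios nearly 3 and 3; design effect 2.5; 95% confidence (z = 1.96); margin d = 0.10; expected total 700, which over four arms is 700/4 = 175 per arm.

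**Formula.** n = 2.5 × 1.96² × p(1−p) / d². Here 2.5 × 1.96² = 9.604.

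**Reproducing the protocol's figures**

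- p = 2 × 0.108 = 0.216 and p(1−p) = 0.216 × 0.784 = 0.1693. Then n = 9.604 × 0.1693 / 0.01 = 162.6, rounded up to **163**. This matches.
- Half-width at 700: √(9.604 × 0.1693 / 700) = 0.048, or **4.8 points**. This matches.

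The formula and inputs are therefore the protocol's own.

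**Changing only the ratio**

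| Ratio | p | n per arm for ±10 points |
|---|---|---|
| 1 | 10.8% | 93 |
| 1.5 | 16.2% | 131 |
| 2 (protocol) | 21.6% | 163 |
| 2.5 | 27.0% | 190 |
| 3 (cited) | 32.4% | 211 |
| maximum | 50% | 241 |

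At ratio 3: p(1−p) = 0.324 × 0.676 = 0.2190, so n = 9.604 × 0.2190 / 0.01 = 210.3, rounded up to 211. Over four arms that is 844 men, against 4 × 163 = 652. If nearly three is read as 2.8 to 2.9 (an assumed range), n is 203 to 207.

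**Precision with the men expected**, half-width = √(9.604 × p(1−p) / n)

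| p | 163 per arm | 175 per arm | 700 pooled |
|---|---|---|---|
| 10.8% | 7.5 | 7.3 | 3.6 |
| 21.6% | 10.0 | 9.6 | 4.8 |
| 32.4% | 11.4 | 11.0 | 5.5 |
| 50% | 12.1 | 11.7 | 5.9 |

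(in percentage points)

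**Slack in the design.** With 175 per arm, ±10 points requires p(1−p) ≤ 175 × 0.01 / 9.604 = 0.182, that is p ≤ 24.0%. This corresponds to a ratio of 24.0/10.8, about 2.2. The surplus of 12 men per arm over 163 covers only a small departure above two.

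**The case against.** - **163 is not miscalculated.** Correct: it is right for 21.6%. The error lies in the statement about what happens if 21.6% is wrong.
- **The statement is true below two.** It is: a ratio of 1 needs 93 per arm and 1.5 needs 131. But the sentence is not limited to that case, and neither of the two cited HIV ratios is below two.
- **The three-fold ratio may not transfer.** The protocol says that no Kenyan study exists, that it knows of none elsewhere in Africa, and that its sources are from developed countries. Taking two rather than three is a defensible planning judgement, and 32.4% is a sensitivity value rather than an established one. That uncertainty argues for showing a range, not for a one-sided assurance.
- **The 4.8 points are stated for 21.6%.** So they are, and that conditional figure stands. The pooled half-width stays below 6 points at any prevalence.
- **The per-arm figure drives little.** Aim 2 concerns one overall proportion, no per-arm HIV comparison is described in the analysis section, and samples are to be taken from every decliner who consents. This limits the practical harm. The protocol nevertheless sets its ±10-point target per arm, and that target is missed at the cited ratio.
- **A smaller design effect would remove the miss.** At 2.0 and 32.4%, n = 2 × 1.96² × 0.2190 / 0.01 = 168.3, or 169, which 175 meets. A design effect of 2.5 with about 700/45 = 15.6 men per cluster implies an intra-cluster correlation near 1.5/14.6 = 0.10, whereas the only value in the protocol is 0.005, for uptake. But the protocol chose 2.5, and a different design effect would not make the direction-of-error statement correct.

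**Conclusion.** The concern holds. At a fixed absolute margin and prevalences below 50%, a true ratio above two makes the required sample larger than calculated, so the claim that an error falls on the safe side is false in the direction of the cited evidence.

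At a ratio of three the requirement is 211 per arm instead of 163. The per-arm half-width is 11.0 points with 175 men or 11.4 with 163, and the pooled half-width at 700 is 5.5 instead of 4.8. The loss is about 1.0 to 1.4 points against the per-arm target and 0.7 point pooled. This is a modest loss of precision, and the pooled estimate remains usable throughout.

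The figures rest on the protocol's formula, its design effect of 2.5, its 10.8% base rate, an equal split of 700 over four arms, and taking the cited ratio as three.

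**What to change.** Delete the statement that an error in the two-fold assumption errs on the side of safety, and stop describing that ratio as conservative for sample size. Then either:

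- state precision at the three-fold value: ±5.5 points with 700 men and about ±11 points per arm; or
- give the range for prevalences from 10.8% to 50%: ±3.6 to ±5.9 points with 700 men, and ±7.3 to ±11.7 points with 175 per arm.

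The cost is a few sentences and a slightly less favourable stated precision. Enrolment, procedures and analysis are unchanged.

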**Sample size Determination**

Sample size for detecting the impact of the interventions on VMMC uptake

Unpublished data from an on-going demand creation study and an HIV community based study show an average of 30% circumcision prevalence in the target group (25-39 years); a corresponding refusal rate of 15% and loss to follow-up of 15%. Using an average MC uptake of 30%, an intra-cluster correlation coefficient (ICC) of 0.005, and a design effect of 2.5 in sample size formula for cluster studies, we estimated that in order to be able demonstrate at least a 33.3 % increase in the rate of VMMC among young adult men in intervention arms when compared to those in control arm with 80% statistical power, and Bonferroni adjusted two-sided $\alpha=(\frac{0.05}{3})=0.017$ following the implementation of study interventions , we will need a sample size of 4,932 men reached with the intervention.

The graph below (*Figure 1)* shows that an effect size equal to 33.3% increase in MC from 30% to 40% will require about 1233 participants per study arm (total 4932), while an effect size equal to 50% increase in VMMC from 30% to 45% will require 573 participants per study arm (total 2292).

Adjusting for refusal rate of 15% and a loss to follow up of 15%, suggests contacting 1603 per study arm resulting in a total of 6412 uncircumcised men aged 25-39 years.

Fig.1 shows a range of sample size requirements for detecting various percentage increases (effect sizes) in VMMC uptake due to the interventions assuming causal effect, and for an 80% power, a 1.7% significance level and a two sided test.

[figure not shown]

Figure 1: Sample Size Vs Percentage Increase in MC Uptake

Selection of Clusters (Locations):

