## Sub-study 2 Inclusion/Exclusion Criteria

Inclusion*:*

- Be a male aged 25-39
- Resident of one of the 45 study Locations
- Already enrolled in TASCO study (Main study)
- Has declined HIV testing
- Has consented to unlinked testing of his blood from the bleeding vessels/finger prick
- Sought services at a participating VMMC clinic.

Exclusion*:*

- Males outside the 25-39 age bracket
- Non-resident of one of the 45 study Locations
- Not enrolled in TASCO study
- Has accepted linked HIV testing
- Has not consented to unlinked testing of his blood from the bleeding vessels/finger prick.

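### The HIV sub-study multiplies a test-refusal rate defined among men who accept VMMC by all 4,932 participants; the plan's own uptake gives about 262 samples, not 700, and the stated ±4.8 points is not delivered.

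*Protocol*

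**What the plan says.** The sample-size text for the HIV prevalence sub-study, in the Protocol section on HIV testing of participants with unknown status, takes its refusal rate from programme data: "23.6% of the men in the target age-group who accept VMMC decline HIV-testing". It applies that rate to the whole main study ("of the 4932 participants in the main study we expect 1164 (4932*0.236) to refuse HIV testing") and continues: "With assumed unlinked HIV testing acceptance rate of 60%, we can obtain 700 such men from our sample size of 4932 in the main study". The precision follows as "4.8%=sqrt[(2.5*1.96^2*.216*.784)/700". The same text sets a per-arm requirement for estimating prevalence to within 10 points with 95% confidence: "we will need to test randomly selected unlinked blood samples from 163 men per arm whose HIV status is unknown".

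What 4,932 stands for is set in Sample size Determination: "we will need a sample size of 4,932 men reached with the intervention". That is 1,233 per arm, with uptake planned to rise from 30% to 40%.

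Eligibility is in Sub-study 2 Inclusion/Exclusion Criteria: the man must be enrolled in the main study, have declined HIV testing, and meet the condition "Sought services at a participating VMMC clinic". Under Methods/Procedure, blood is taken from bleeding vessels during surgery, or by finger prick after surgery while the man is still in theatre.

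The Abstract uses 4,932 differently, as the number of men expected to take up VMMC. The figure of 700 is repeated in the Abstract and in Methods/Procedure.

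**The concern.** A rate that is conditional on accepting VMMC has been multiplied by a group of whom 60% to 70% are planned not to be circumcised. Those men never reach the clinic test that they could decline, and neither collection route can obtain blood from them. The base should be expected circumcisions.

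The precision of the HIV aim is at stake. The protocol intends to change counselling if prevalence among decliners proves significantly higher than among acceptors (10.8% in programme data). At the planned 21.6% the smaller sample would still separate the two. With a smaller true excess it may not. As an illustration only, assume 16.2% (1.5 times 10.8%), a design effect of 2.5, and 10.8% taken as known. Then 700 samples give ±4.3 points (11.9% to 20.5%), which excludes 10.8%, while 262 give ±7.1 points (9.1% to 23.3%), which includes it. A finding of no difference could then be read as reassurance.

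**Working it through.** **Inputs, all from the Protocol.** Refusal 0.236 among men who accept VMMC; consent to unlinked testing 0.60; assumed prevalence 0.216; design effect 2.5 (all from the sub-study sample-size text). From Sample size Determination: 1,233 men per arm, uptake 0.30 in control and 0.40 in each of three intervention arms, 6,412 men contacted.

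**Formulas.** Samples = circumcised men × 0.236 × 0.60 = circumcised men × 0.1416. Half-width = √(design effect × 1.96² × 0.216 × 0.784 / n), the plan's own formula.

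**The plan's figures reproduce.**
- 4,932 × 0.236 = 1,164; × 0.60 = 698, stated as 700.
- Half-width at n = 700: 4.82 points.
- n for ±10 points: 2.5 × 1.96² × 0.216 × 0.784 / 0.10² = 162.6, stated as 163.

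**With expected circumcisions as the base.**
- Circumcised: 1,233 × (0.30 + 3 × 0.40) = 1,849.5.
- Declining the test: 1,849.5 × 0.236 = 436.5.
- Consenting: 436.5 × 0.60 = 261.9, about 262.
- Half-width at 262: 7.9 points at design effect 2.5; √(1.96² × 0.216 × 0.784 / 262) = 5.0 points at design effect 1.

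**Per arm, design effect 2.5.**
- Control: 1,233 × 0.30 × 0.1416 = 52.4 samples, ±17.6 points.
- Each intervention arm: 1,233 × 0.40 × 0.1416 = 69.8 samples, ±15.3 points.
- To reach 163, an arm needs 163 / 0.1416 = 1,151 circumcisions among 1,233 men, or 93% uptake.

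**Sensitivity, design effect 2.5.**

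| Assumption | Samples | Half-width (points) |
|---|---|---|
| 30% uptake in all arms | 210 | 8.8 |
| 40% uptake in all arms | 279 | 7.6 |
| 30% control, 45% intervention | 288 | 7.5 |
| All 6,412 contacted, 37.5% average uptake | 340 | 6.9 |
| 1,849.5 circumcised, refusal 10% | 111 | 12.1 |
| 1,849.5 circumcised, refusal 30% | 333 | 7.0 |

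The last two rows use the 10% to 30% refusal range that opens the HIV testing section. Reaching 700 needs 700 / 0.1416 = 4,944 circumcised men: slightly more than all 4,932 participants, or 77% of the 6,412 contacted.

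**The case against.** The strongest reply is the Abstract. If 4,932 men take up VMMC, then 4,932 × 0.1416 = 698 and the paragraph is coherent. The accrual estimate of 822 eligible men a month also gives 4,932 over six months, although that text does not say clearly whether they are clients or enrolled men. This shows that the document uses 4,932 in two senses. It does not rescue 700: in Sample size Determination 4,932 is the denominator of the uptake proportion, and 4,932 circumcisions among 6,412 contacted men would be 77% uptake against a planned 30% to 40%.

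Second, ±7.9 holds the design effect at 2.5 although the sample per Location falls from 700/45 = 15.6 to 262/45 = 5.8. This stands. If 2.5 is assumed to apply at 15.6 per Location, the implied intra-cluster correlation is 1.5/14.6 = 0.103, the design effect at 5.8 is 1 + 4.8 × 0.103 = 1.5, and the half-width is about ±6.1. Even with no clustering it is ±5.0, so ±4.8 is still missed.

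Third, 262 depends on planning values. This also stands. The 30% first appears as a circumcision prevalence, and refusal may differ from 23.6%. Other features of the plan would lower the yield: men circumcised at non-study clinics, men who cannot be matched at the clinic, and the three-month window for capturing circumcisions.

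Fourth, neither Aim 2 nor the planned HIV analysis asks for prevalence by arm, so the per-arm shortfall breaks a stated requirement but no planned comparison.

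**Conclusion.** The point holds. The arithmetic reproduces, but the base is wrong for a rate defined among men who accept VMMC. On the plan's own inputs the expected yield is about 262 samples, and none of the uptake, refusal or follow-up scenarios above exceeds about 340. The stated ±4.8 points is not delivered: it becomes about ±7.9 at design effect 2.5, or ±5.0 at the most favourable. The count of 163 is missed in every arm. These sizes rest on 30%/40% uptake, 23.6% refusal and 60% consent.

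Three stronger readings should be avoided:
- A reader might infer that the sub-study misses every precision it names. It does not: ±10 points is also stated, and the pooled ±7.9 lies within it. At 10% refusal, however, the pooled figure would be ±12.1.
- A reader might infer that the trial's main comparison is weakened. Its alpha, power and cluster numbers do not depend on this calculation.
- A reader might infer that unlinked results cannot be tied to an arm, so that non-enrolled clients could make up the shortfall. The sample request form records Location, and Table 3 assigns each Location to an arm. The criteria also restrict the sub-study to enrolled men.

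This should be fixed, but it is confined to the HIV sub-study.

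**What to change.** - Reconcile the meaning of 4,932 in the Abstract, Sample size Determination and the sub-study sample-size text.
- Compute the yield as expected circumcisions × 0.236 × 0.60, and replace 700 with about 262 in the Abstract, the sub-study text and Methods/Procedure.
- Restate the pooled precision as about ±8 points at design effect 2.5. Show the uptake, refusal, consent and design-effect assumptions and the range beside it, so that 262 is not read as a firm figure.
- Withdraw the 163-per-arm claim.

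The cost is rewording and a less favourable stated precision. Eligibility, sampling and the main trial are unchanged.

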**Methods:** We will employ cluster-randomized controlled design. Through elimination by factors such as proximity to circumcising communities, multi-ethnic urban populations, and geographical proximity to each other, 45 administration Locations in Nyanza Province have been selected and randomized into IPC implemented alone, DSO implemented alone, IPC and DSO implemented together and control. Under IPC, we will develop a Toolkit for Addressing Barriers and Facilitators to VMMC with messages that address barriers to and reinforce facilitators of VMMC, and engage behavioral counselors to deliver intervention massages that are custom-made to address participants’ specific issues; Under DSO, selected facilities, days and hours will be set aside to serve only men aged ≥25 years; these sites will be served by older, male providers only; Under Combined IPC and DSO, the effect of both interventions implemented together will be examined; and in the Control locations, no intervention will be implemented. Altogether, 4,932 men aged 25-39 years are expected to take up VMMC during the study period, which will take up to nine months.

For aim 2, we will collect blood samples from bleeding vessels of an estimated 700 men whose HIV status is unknown, and perform unlinked test for HIV at the KEMRI/CDC HIV Laboratory in Kisumu. For aim 3, we propose to extract from our procurement, stores and accounts records expenditures for demand creation and service delivery.

To augment this study, we will nest a sub-study (sub-study 4) in all the 45 study Locations and enroll approximately 720 men who are in stable sexual relationships, together with their partners, for post circumcision follow up visits to monitor the impact of involving female partners on time to resumption of sex post-surgery.

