## Enrollment of Sub-study Participants:

Participants for sub-study 3 will be enrolled from all the 45 Locations; however the Locations will be randomly assigned into nine (9) groups each with five clusters. Leaving the first two weeks to allow for the study set up and, have it up and running smoothly, and the last month for close out, enrollment into the study will take place over the remaining four and a half months (18 weeks). The first group will be assigned the first two weeks (i.e. week 3 & 4) to enroll the first 16 consenting participants; the next group of five clusters will be assigned the next two weeks (i.e. week 5 & 6) to enroll their participants and the process repeated until all the 45 clusters have been assigned their two-week enrollment period (ending week 19 & 20). After this period, enrollment will be opened for a further two weeks to all the clusters who will not have achieved the enrollment target. We believe that since each Location will be enrolling only 16 participants, the proposed arrangement allows for adequate time to enroll all the sub-study 3 participants and for enrolment to spread throughout the data collection period.

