**Estimated study participant accrual period**

Following a review of recruitment data from numerous studies of VMMC (IRDO program data) that we have previously conducted in several sites in the study area some of which have been selected for study implementation in this application, we estimate a conservative average study-wide combined accrual rate of 822 eligible men (25-39 years) per month across the 45 sites (18-19 men per Location per month).

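### The HIV sub-study's 700 samples are computed from all 4,932 men reached, with no factor for uptake; at the plan's own uptake about 262 are expected, so the stated precision needs restating

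*Protocol*

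**What the plan says.** The sub-study sample size, under the heading on HIV testing of participants with unknown status, makes two statements.

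- **Requirement.** "we will need to test randomly selected unlinked blood samples from 163 men per arm", to estimate prevalence to within 10 points with 95% confidence, assuming 21.6% prevalence and a design effect of 2.5.
- **Expected yield.** "of the 4932 participants in the main study we expect 1164 (4932*0.236) to refuse HIV testing". With 60% of these consenting to unlinked testing, "we can obtain 700 such men from our sample size of 4932 in the main study", for a pooled precision of 4.8 points.

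The same section gives 23.6% as the proportion declining a test among men in the age group who accept circumcision. The sub-study inclusion criteria require that the man "Sought services at a participating VMMC clinic". Methods/Procedure takes the vessel sample during surgery, and the alternative finger-prick sample after surgery while he is still in theatre.

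The protocol describes 4,932 in two ways. Sample size Determination says "we will need a sample size of 4,932 men reached with the intervention", at 1,233 per arm, to detect a rise in uptake from 30% to 40%. The Abstract says "4,932 men aged 25-39 years are expected to take up VMMC during the study period".

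**The concern.** Both rates in the yield calculation apply to men who present for circumcision. The number they multiply is, by the main sample-size section, the denominator of the uptake comparison, and the plan expects most of those men not to be circumcised. The uptake factor is missing, so the expected sample is overstated.

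This matters because HIV prevalence in men of unknown status is one of the three numbered aims, and the protocol says the result will affect how men who refuse testing are counselled. Reviewers and ethics committees are shown a sample size and a precision that the plan's own assumptions do not deliver.

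**Working it through.** **Inputs, all from the protocol.** 4,932 men, 1,233 per arm, uptake 30% (Control) and 40% (three intervention arms), ICC 0.005, from Sample size Determination. Declining rate 0.236, consent 0.60, prevalence 0.216, design effect (DE) 2.5, from the sub-study sample size. 45 Locations, 11 or 12 per arm, from the randomization tables.

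**Reproducing the stated figures.**
- Combined rate: 0.236 × 0.60 = 0.1416 (stated 14.2%).
- Yield: 4,932 × 0.1416 = 698 (stated 700).
- Half-width = √(DE × 1.96² × 0.216 × 0.784 / n). With DE 2.5 and n = 700: 4.8 points, as stated.
- Per-arm requirement: 2.5 × 1.96² × 0.216 × 0.784 / 0.10² = 162.6, i.e. 163, as stated.

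The arithmetic is right, but the base is wrong.

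**Adding uptake.**
- Circumcised: 1,233 × 0.30 + 3 × 1,233 × 0.40 = 369.9 + 1,479.6 = 1,849.5.
- Samples: 1,849.5 × 0.1416 = 262.
- By arm: Control 1,233 × 0.30 × 0.1416 = 52; each intervention arm 1,233 × 0.40 × 0.1416 = 70.

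**Precision at the plan's DE of 2.5.**

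| | n | Half-width (points) | Stated |
| --- | --- | --- | --- |
| Pooled | 262 | ±7.9 | n 700, ±4.8 |
| Control | 52 | ±17.6 | n 163, ±10 |
| Each intervention arm | 70 | ±15.3 | n 163, ±10 |

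**Range of the yield.**
- 30% uptake in all arms: 1,479.6 × 0.1416 = 210 (±8.8 at DE 2.5).
- 40% in all arms: 1,972.8 × 0.1416 = 279 (±7.6).
- 6,412 contacted less 15% refusal = 5,450 enrolled, at 37.5% average uptake: 289 (±7.5).
- All 6,412 enrolled, same uptake: 340 (±6.9).
- 100% consent to unlinked testing, base 4,932: 1,849.5 × 0.236 = 436.
- Declining rate of 10% to 30%, the range quoted at the start of the section: 111 to 333.

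None reaches 700. To obtain 163 in an arm, 163 / 0.1416 = 1,151 of 1,233 men (93%) would have to be circumcised.

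**A design effect matched to the expected cluster size.** 262 / 45 = 5.8 samples per Location. With DE = 1 + (m − 1) × ICC:
- ICC 0.005 (the protocol's value, given for uptake): DE = 1 + 4.8 × 0.005 = 1.02; pooled ±5.0.
- ICC 0.1 (my assumption for an upper value): DE = 1 + 4.8 × 0.1 = 1.48; pooled ±6.1.
- Per arm with 11 Locations: Control (m = 4.8) ±11.2 to ±13.1; intervention (m = 6.3) ±9.8 to ±12.0.

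**The case against.** **The Abstract's reading.** If 4,932 men really take up circumcision, 700 follows. The accrual section might be read in support: it gives 822 eligible men a month ("18-19 men per Location per month"), and 822 × 6 = 4,932. But that section counts eligible men, and eligible men are uncircumcised at entry. Taking 4,932 as circumcisions means 100% uptake of the sample-size denominator, or 4,932 / 6,412 = 77% of the men to be contacted, against a planned 30% to 40%. At 37.5% average uptake it would need 4,932 / 0.375 = 13,152 enrolled men. The contradiction is real and the sponsor must resolve it, but the Abstract's wording does not rescue 700 alongside the main sample size.

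**Per-arm precision.** A reader might infer that ±10 points per arm is out of reach. That holds only at a design effect of 2.5. At the protocol's ICC and about 6 samples per Location, the intervention arms reach ±9.8 and Control ±11.2, and the requirement falls from 163 to about 67. This part of the objection stands.

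**Whether the aim survives.** It does. Aim 2 asks for one proportion, and even ±7.9 pooled lies within 10 points.

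**The two-week enrolment windows.** The section on enrolling sub-study participants gives each group of Locations a fortnight "to enroll the first 16 consenting participants". A reader might infer that this caps HIV sampling and cannot be met at the stated accrual. The documents do not support that. The paragraph is labelled sub-study 3 (elsewhere the costing sub-study) and does not mention HIV or blood. Its 16 × 45 = 720 equals the target for sub-study 4. The sub-study sample-size text opens sampling to all men who refuse testing and consent. What remains is a labelling or placement problem.

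**Conclusion.** The expected yield of 700 and the precision of 4.8 points are wrong as written: rates defined among men accepting circumcision are applied to all men reached. Under the main sample-size assumptions the expected number is about 262, an overstatement of about 2.7-fold (700 / 262). The plausible range is 210 to 279 on a base of 4,932, and about 290 to 340 if the enrolled base is nearer 6,412. The lower figures may be generous, since the endline section expects some men to use non-study clinics, where they would not meet the sub-study criteria.

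How much precision is lost depends on the design effect. It is substantial at the plan's 2.5 and modest for the pooled estimate at 1.0 to 1.5. The upper end of that lower range rests on an assumed ICC of 0.1, because the protocol gives no ICC for HIV status. The point is therefore a stated sample size and precision that need correcting. It does not show that the aim is unattainable, and it leaves the primary outcome untouched.

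**What to change.** 1. Reconcile the Abstract, Sample size Determination and the sub-study calculation on whether 4,932 is men reached or men circumcised.
2. Put the uptake factor into the yield and restate the expected number: about 260 if the main sample-size section is kept, with a range.
3. Recompute the pooled precision with a design effect matched to the expected samples per Location, and state the ICC assumed.
4. Replace the 163-per-arm figure with the recomputed per-arm precision, or report only the pooled prevalence.
5. State which sub-study the 16-per-Location, two-week enrolment paragraph governs, so that its windows are not applied to HIV sampling by mistake.

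The cost is wording and a less favourable stated precision. No extra participants are needed.
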